#### Sensitivity analyses

To assess the robustness of our ITT primary analysis with possible missing data we will repeat the primary analysis using completers data only as well as per-protocol data only, using multiple imputation method to generate missing data in the stratification step. To assess the impact of participant-level factors on the primary outcome we will examine DFS separately in those who, at study end, have reached normo-glycemia (<110 mg/dl) and normal levels of HbA1c <6.0% versus those who have higher levels, in those who reached circulating 25(OH)D ≥60 ng/ml versus those who reached ≤30 ng/ml, in those who have lower versus those who have higher insulin levels (median will be used as cut-offs), in those who have good overall compliance on the three treatment components that is in the highest quantile of: low GI + number of daily steps + levels of 25(OH)D, versus those who have lower compliance. For these analyses study end is defined as the mean of the last three visits.

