**Fig. 1 Fig1:**
[figure not shown]
Schematic representation of DEDiCa study protocol

To improve compliance participants on both sides will be followed equally with blood tests and clinic visits and will be equally offered general advice on a healthy Mediterranean diet and physical activity, step counters and vitamin D supplements to avoid insufficiency. Participants in the HIT group will additionally receive dietary counselling on how to reduce the GI of their diet, packages of pasta, more in-depth advice on exercise and more vitamin D supplements compared to the LITE group.

This study was approved by the ethic board of the Italian Medicine Agency (AIFA), and of each recruiting hospital: National Cancer Institute “Fondazione Giovanni Pascale” in Naples, Azienda Ospedaliera per l’Emergenza Ospedale Cannizzaro in Catania, Azienda Ospedaliera Universitaria Policlinico “G. Martino” in Messina for San Vincenzo Hospital of Taormina, Comitato Etico Campania Centro ASL NA1 Centro for Clinica Mediterranea in Naples. The study has been registered with ClinicalTrials.gov (registration date and number: May 11, 2016; NCT02786875).

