#### Primary analyses

The primary analyses will assess the between-treatment difference in BC recurrence measured as disease-free survival (DFS), calculated as the percentage of patients alive without recurrence of disease at study end (up to 33 months from randomization). BC recurrence is defined as the relapse of the disease or metastasis either in the same breast (including new positive lymph nodes), or the opposite breast or in distant organs. The duration of DFS in patients lost at follow-up will be censured at the date of the last day the patient was considered free of disease. Between-treatment differences in DFS will be analyzed by *log-rank* test. Kaplan-Meier curves will be provided to estimate median DFS and 95% CI. To address the impact of potential imbalance in prognostic factors we will repeat the primary analysis using the *log-rank* test stratified by stage, age, family history of BC, time since diagnosis, molecular subtype, medication use, smoking, baseline waist circumference and dietary variables (baseline GI, dietary fiber, saturated fat, vegetables/fruit, meat, sweets/desserts). Missing data for covariates will be handled by using the missing indicator method.

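### The planned missing-data check repeats the analysis in completers and per-protocol women and never varies what happened to women after loss, so agreement with the ITT result gives no reassurance

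*Protocol article*

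**What the plan says.** Under Primary analyses, the protocol article defines DFS as a percentage at study end and compares the arms by log-rank test. Women lost to follow-up are censored when they were last known to be disease-free. A supportive repeat uses a log-rank test stratified by a long list of prognostic and dietary variables. For that repeat, "Missing data for covariates will be handled by using the missing indicator method".

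Under Sensitivity analyses, the aim and the method are both fixed: "To assess the robustness of our ITT primary analysis with possible missing data we will repeat the primary analysis using completers data only". A second repeat is restricted to per-protocol women, and imputation is assigned to one place: "using multiple imputation method to generate missing data in the stratification step". The other analyses in that section split women by glucose, HbA1c, vitamin D, insulin or compliance reached at study end. None of them concerns loss. Nothing in the article assigns or varies the outcome of a woman after she is lost.

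**The concern.** The primary test already counts each lost woman as at risk until her last disease-free date. It is valid if, within each arm, women who leave have the same later recurrence risk as women who stay. A missing-data check should stress that assumption. A completers analysis discards the women in question, and it needs a stronger assumption than the primary analysis does. Covariate imputation can affect only a stratified test.

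Loss could plausibly differ by arm. Over up to 33 months, HIT asks for a changed diet and additional daily walking. It also receives "packages of pasta, more in-depth advice on exercise and more vitamin D supplements compared to the LITE group". These features pull in opposite directions, so the direction of any difference is unknown. If the two analyses agreed, the report could call the result robust to missing data on evidence that does not bear on the question.

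A smaller issue is that, in the stratified repeat, the check changes the population and the covariate method together (missing indicator to multiple imputation). A changed stratified result could not be traced to either one.

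**Working it through.** **Inputs from the article.** Recurrence of 20% in control and 10% in HIT, the 20% being stated within 3 years; 253 women per arm; follow-up to 33 months; lost women censored. The article gives no loss rate and no figure for this check, so there is no planned number to reproduce. Loss rates and post-loss hazards below are assumptions.

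**Rates at 33 months (constant hazard).**
- LITE: 1 − 0.80^(33/36) = 18.5%.
- HIT: 1 − 0.90^(33/36) = 9.2%.
- Hazard ratio: ln(0.90)/ln(0.80) = 0.47.

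**1. Does the check respond to what happens after loss?** Large-sample simulation (at least 400,000 per arm), exponential event times, 20% of HIT and 5% of LITE assigned a loss time uniform over 33 months. After loss, the HIT hazard is multiplied by k.

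| k | True HR | Primary (censored) | Completers |
|---|---|---|---|
| 1 | 0.47 | 0.47 | 0.51–0.52 |
| 3 | 0.56 | 0.47 | 0.51–0.52 |
| 5 | 0.64 | 0.47 | 0.51–0.52 |

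The last two columns are constant by construction, because the observed data are the same in every row.

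**2. Does the check move when nothing is wrong?** Take 15% risk at 33 months in both arms and harmless loss at uniform times. A woman assigned a loss time has, on average, about half the 15% risk (7.5%) before it and half after it.
- HIT, 20% assigned: lost 0.20 × (1 − 0.075) = 0.185; observed events 0.15 − 0.20 × 0.075 = 0.135; completers' risk 0.135/0.815 = 0.166.
- LITE, 5% assigned: lost 0.05 × 0.925 = 0.046; observed events 0.15 − 0.05 × 0.075 = 0.146; completers' risk 0.146/0.954 = 0.153.
- HR ≈ ln(1 − 0.166)/ln(1 − 0.153) ≈ 1.09.

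Simulation gives 1.08 to 1.09, and 0.91 to 0.92 with the loss rates reversed. The primary analysis stays at 1.00 within simulation error. The shift arises because every observed event is kept while only event-free women are removed.

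**3. Does agreement reassure?** No true effect, 253 per arm, 20% three-year risk, 10% harmless loss in both arms. In addition, a share q of HIT women who recur are lost within 3 months before the recurrence is recorded.

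| q | False positives, primary | False positives, completers | Completers agree when primary is falsely positive |
|---|---|---|---|
| 0 | 5% | 5% | not run |
| 20% | 16% | 14% | 84% |
| 30% | 35% | 31% | 86% |
| 50% | 79% | 71% | 92% |

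**4. What would a varied outcome show?** Assume 10% vs 20% risk among women followed, equal loss in both arms, and 20% risk in lost LITE women. With 20% loss, 51 per arm are lost and 202 followed.
- Completers: z = 0.10/√(0.15 × 0.85 × 2/202) = 2.81, whatever happened to the lost women.
- All women, risk 28% in lost HIT women: HIT events 0.10 × 202 + 0.28 × 51 = 34.5; LITE events 0.20 × 253 = 50.6; pooled risk 85.1/506 = 0.168; z = (16.1/253)/√(0.168 × 0.832 × 2/253) = 1.92.

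Significance is therefore lost at about 28%. The same calculation gives about 46% with 10% loss and 34% with 15% loss.

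**The case against.** - **No analysis of the observed data can detect informative loss.** This stands. A reader might infer that the completers analysis fails where a better method would detect the problem, but delta-adjusted imputation does not detect it either. It shows how bad the loss would have to be. The supportable point is that the named check never varies the assumption at risk.
- **The illustration is severe.** Also fair. At 253 per arm with 20% vs 5% loss and all outcomes known, the mean log-rank z is −3.03, −2.47 and −1.95 for k = 1, 3 and 5. With 15% vs 10% loss it is −2.22 even at k = 5. The completers shift under no effect raises the two-sided rejection rate only to about 6–7%. The documents do not support reading this as a prediction that the trial's conclusion would be wrong.
- **Retention measures are equal.** Both arms have the same visits and blood tests, step counters and general advice, and the recruitment section provides for regular telephone contact. Recurrence is assessed by the centre's oncologist and confirmed by pathology, so leaving the program need not mean losing the outcome. This lowers the likely loss but does not make the check informative about whatever loss occurs.
- **Detail belongs in a fuller plan.** A delta grid would normally be left to the analysis plan. But the article does not leave the method open: it names one that does not serve the stated aim.
- **Two further inferences fail.** One is that a completers analysis would delete deaths; the term is not defined, so this is conjecture. The other is that the primary test uses an inconsistent covariate method; the missing-indicator method belongs to the stratified repeat, and the primary log-rank test is described without strata.

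**Conclusion.** The concern holds in a limited form. The stated check removes lost women and, on its natural reading, imputes only stratification covariates. If outcomes were meant to be included, standard multiple imputation would still assume missing at random and leave the key assumption unvaried. Agreement between the completers and ITT results is therefore no evidence of robustness. Disagreement may reflect nothing more than harmless differential loss, about 8–9% on the hazard ratio under the assumed 20% vs 5%. How much this matters depends on loss rates and post-loss hazards that the documents do not give. On the assumptions used, the risk in lost HIT women at which significance is lost ranges from about 46% (10% loss) to 28% (20% loss). This should be changed, but it is not a flaw in the primary test itself.

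**What to change.** Make the missing-data sensitivity analysis an imputation of DFS time after loss for all randomized women censored before month 33. Vary the post-loss hazard by arm over a pre-set grid of multipliers (for example 1, 1.5, 2, 3 and 5 in HIT, with LITE at 1 and then varied too). Include a version in which lost HIT women take the LITE hazard. Report the multiplier at which the conclusion changes, and the loss by arm with reasons. Keep the completers and per-protocol repeats as supplementary analyses, not as the evidence on missing data.

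Counting every lost woman as an event is not a sufficient substitute. In the simulation of step 3 it held the false-positive rate near 5–6% when background loss was equal, but gave about 18–19% with 5% vs 10% background loss.

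In the stratified repeat, use the same covariate-missingness method as in its sensitivity version, so that population and method do not change together.

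The cost is revised wording and modest programming, with no new data. The result may look less robust than the completers comparison would suggest.

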### Sample size

Considering a 20% recurrence rate within 3 years in most collaborating centres for BC cases specified in Table 2, and a predicted rate of 10% in the high intensity arm, with power of 80% and two-sided alpha of 0.05, the number of subjects are 506 (*n* = 253 in each arm).

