#### Secondary analyses

The mean and standard error for each of the following variables will be determined for each study group. The change from baseline to end of study will be compared between groups using repeated measures ANOVA and using nonparametric tests if necessary, for the following variables: body weight, waist circumference, BMI, blood pressure, serum levels of 25(OH)D, blood glucose, HbA1c, insulin, IGF-1, lipids, CRP, estradiol, testosterone, SHBG, specific microRNAs, dietary glycemic index, number of steps per day and quality of life. We will also test treatment differences in medication use and medication side effects. Chi-square test will be used to compare categorical variables and Student t-test or Wilcoxon test for continuous variables. The association between each variable and prognosis will be analyzed using Cox proportional hazard model and logistic regression. Finally, we will assess whether these secondary analyses are different at year 1 compared to end of study. All statistical analyses will be conducted with SPSS statistical software version 23.0 (SPSS Inc., Chicago IL, USA).

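### DFS is related to combined compliance only as top quantile versus the rest, and to insulin by a median split; a full-scale Cox model would keep the third to a half of the information that these cuts discard (minor).

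*Protocol article*

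**What the plan says.** Under Sensitivity analyses, the protocol article sets out a group of participant-level analyses: "To assess the impact of participant-level factors on the primary outcome we will examine DFS separately in those who, at study end", have or have not reached certain levels. For glucose, HbA1c and 25(OH)D the groups are defined by stated thresholds. Two contrasts are instead defined by the distribution in the sample:

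- Insulin: "in those who have lower versus those who have higher insulin levels (median will be used as cut-offs".
- Overall compliance with the three components: "that is in the highest quantile of: low GI + number of daily steps + levels of 25(OH)D, versus those who have lower compliance". Which quantile is meant is not stated.

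The values to be grouped are averages: "For these analyses study end is defined as the mean of the last three visits".

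Secondary analyses then adds, for a list that includes insulin, 25(OH)D, dietary GI and daily steps: "The association between each variable and prognosis will be analyzed using Cox proportional hazard model and logistic regression". The combined compliance measure is not on that list, and the form in which each variable enters the model is not given.

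**The concern.** The Interventions section describes food records that yield daily mean GI, a step counter with a 7-day memory and repeated serum 25(OH)D. Insulin is a laboratory value. Cutting such measures into two groups before relating them to DFS treats a woman just under the cut like one who followed none of the programme, and ignores all differences within each group. No reason for either cut is given.

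The compliance contrast matters more. The intervention is a three-component package, so whether DFS improves with the degree of combined adherence is the dose-response question closest to the trial's hypothesis, and the article plans no other analysis of it. With few recurrences expected, a coarse grouping gives an imprecise answer that could be read as no relation with adherence.

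**Working it through.** **Inputs from the document.** Sample size gives 20% recurrence within 3 years in the control arm ("Considering a 20% recurrence rate within 3 years in most collaborating centres"), "a predicted rate of 10% in the high intensity arm", and 253 women per arm. Primary analyses gives follow-up of up to 33 months.

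**The plan's own figure.** No power is stated for the compliance or insulin analyses. The only stated power is for the comparison of arms: "with power of 80% and two-sided alpha of 0.05, the number of subjects are 506". The usual two-proportion formula for 20% versus 10% gives 199 per arm (398 in total), or 219 per arm (438) with continuity correction. The 506 is therefore not reproduced without an unstated allowance, and 253 per arm gives about 88.5% power. Nothing below depends on this; only the 506 women and the event rates are used.

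**Expected events (constant hazards).**
- Control: 253 × (1 − 0.8^(33/36)) = 253 × 0.185 = 46.8
- HIT: 253 × (1 − 0.9^(33/36)) = 253 × 0.092 = 23.3
- Total: about 70. Taking the 3-year rates unadjusted, 506 × 0.15 = about 76.

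**Information kept by a cut.** For a normal score with a log-linear effect on the hazard, putting the upper share p in one group keeps the fraction E = φ(z)² / [p(1 − p)], where z is the cut point and φ the normal density.

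**Power.** Take an association that a continuous Cox trend test would detect with 80% power at two-sided 0.05. This benchmark is an assumption, not a protocol figure. Its standardised effect is 1.960 + 0.842 = 2.802. With 70 events this is a hazard ratio of exp(−2.802/√70) = about 0.72 per SD. After the cut, power = Φ(2.802 × √E − 1.960).

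| Cut | E | 70 events worth about | Power, large-sample | Power, simulated |
|---|---|---|---|---|
| None (full scale) | 1 | 70 | 80% | 80% |
| Median | 0.637 | 45 | 61% | 60% |
| Top third | 0.595 | 42 | 58% | 53% |
| Top quarter | 0.539 | 38 | 54% | 45% |
| Top fifth | 0.490 | 34 | 50% | 39% |

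The simulation used 6,000 trials of 506 women with about 15% events, a hazard ratio of 0.723 per SD and the Cox score test. The simulated losses for the top cuts exceed the large-sample ones because the top group is the protected one and contributes few events. With the effect reversed, so that the top group is at higher risk (hazard ratio 1.38 per SD, full-scale power 79.5%), the same cuts gave 61%, 59% and 57%, and the median split again 60%.

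The information lost is thus 36% at the median and 41% to 51% for a top third to top fifth.

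**The case against.** Several points on the other side stand.

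- **Insulin is largely covered already.** Secondary analyses plans a Cox model for it. A reader might infer that insulin is related to DFS only through the median split; the article does not support that. What is open is whether the Cox term is continuous and which analysis carries the inference.
- **No test is named.** For these groups the article says only that DFS will be examined separately. The log-rank test is specified for the difference between treatments. A reader might infer a planned formal test at 40% to 60% power; the document states no test, alpha or power here, and the low end near 40% comes only from simulating a top-fifth cut of a quantile that the text does not define.
- **The benchmark is hypothetical.** The 80% and the normal, log-linear score are assumptions. The arms are steered to different targets, so a pooled score need not be normal, and the loss could be smaller or larger.
- **A nearly empty group is not the natural reading.** One could take good compliance to mean the top quantile on all three components at once; with independent components and thirds, that would leave 506/27 = about 19 women. The plus signs in the definition read more naturally as one composite.
- **The undefined quantile is not itself a finding.** A condensed article may leave it to the full protocol or SAP.
- **A continuous model does not cure the larger limitation.** The values are measured after randomisation, so the association is open to confounding and to influence from the outcome, whatever scale is used.

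None of this supplies a full-scale analysis of the compliance composite, and the choice to analyse it as top group versus rest is written into the plan.

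**Conclusion.** The point holds, mainly for the compliance composite, and is minor. As written, DFS is related to combined compliance only through a cut that keeps about 59% to 49% of the information if the quantile is a third to a fifth. The insulin median split keeps about 64%, but a Cox model for insulin is already planned. Against a hypothetical 80% on the full scale, that means about 58% to 50% power for compliance and 61% for insulin by large-sample theory (53% to 39% and 60% in simulation).

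These figures assume a roughly normal score, a log-linear effect and, for the simulated top cuts, a protective effect. The relative loss of information in the large-sample figures does not depend on the 80% benchmark; a true threshold effect or a skewed score would change it. The analyses are supporting ones. The primary log-rank comparison, the sample size and the data collected are unaffected, and the raw values remain available.

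**What to change.** In Sensitivity analyses:

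1. Make the main compliance analysis a Cox model for DFS with one prespecified continuous score, for example the mean of the three standardised components with GI reversed. Report the hazard ratio per SD with its 95% CI, and check for non-linearity with a spline or quadratic term.
2. State that the Cox model for insulin planned in Secondary analyses uses insulin, log-transformed if skewed, on its continuous scale, and that it replaces the median split as the inferential analysis.
3. Keep Kaplan-Meier curves by compliance or insulin group as description only, without a test.
4. State that all of these are observational associations with post-randomisation values.

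The cost is a few sentences. It needs no new data or patients, and Cox models are already planned in the named software. The downsides are the log-linear assumption, which the non-linearity check addresses, an equal weighting of components that has to be agreed in advance, and an effect per SD that is less intuitive than two curves.

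### The sensitivity analyses compare DFS from randomisation between groups formed by the mean of the last three visits; under no reading of that rule is the comparison valid, and the size and direction of the bias depend on details the article does not give

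*Protocol article*

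**What the plan says.** Under Sensitivity analyses, the protocol article sets out four comparisons of DFS by what women achieved during the trial:

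- Glycaemia: "we will examine DFS separately in those who, at study end, have reached normo-glycemia", together with a normal HbA1c, against women with higher levels.
- Vitamin D: "in those who reached circulating 25(OH)D ≥60 ng/ml versus those who reached ≤30 ng/ml".
- Insulin: "in those who have lower versus those who have higher insulin levels (median will be used as cut-offs".
- Compliance: "in the highest quantile of: low GI + number of daily steps + levels of 25(OH)D, versus those who have lower compliance".

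The same paragraph then fixes the time of measurement: "For these analyses study end is defined as the mean of the last three visits". Under Primary analyses, DFS is "calculated as the percentage of patients alive without recurrence of disease at study end (up to 33 months from randomization", and between-group differences are tested by log-rank. No landmark or time-updated handling is given for the four comparisons.

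Secondary analyses adds: "The association between each variable and prognosis will be analyzed using Cox proportional hazard model and logistic regression". It does not say whether each variable is a baseline value, a change or a final value.

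**The concern.** A log-rank test or hazard ratio is valid only if group membership is known when follow-up starts. Here it is known only later. The last-visits rule can be read in three ways, and each has a fault.

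- **Values end at recurrence.** A woman who recurs at month 6 is judged on months 0, 3 and 6. For markers taken three-monthly, a woman disease-free to month 33 is judged on months 27, 30 and 33. Interventions describes 25(OH)D in the intensive arm as raised towards 60 ng/ml with dose review every three months, so reaching it takes time on study. Staying disease-free is then part of what puts a woman in the better group (immortal-time bias).
- **Visits continue after recurrence.** The values come after the event. Glucose, insulin, steps and diet may then reflect relapse and its treatment (reverse causation).
- **Only the last scheduled visits count.** Women who recurred and left have no value and drop out, which is selection on the outcome.

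Insulin has a further problem. Table 5 lists it only at baseline, 12 months and study end. A completer's last three values are those three. A woman who recurs before month 12 has baseline alone if her values end there.

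The article presents these analyses as showing how participant-level factors affect the primary outcome. A spurious ratio well below 1 at 60 ng/ml could be read as evidence for that target.

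**Working it through.** The article states no figure for these comparisons, so there is none to reproduce. The check asks what the rule yields when no marker has any effect on recurrence.

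**Inputs from the article.** 506 women; visits every 3 months from 0 to 33; DFS from randomisation; log-rank test; 25(OH)D cut-offs of 60 and 30 ng/ml; 3-year recurrence of 20% (control) and 10% (intensive arm). The simulation varies recurrence from 10% to 20%.

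**Assumptions, not in the article.** Constant hazard; mean baseline 25(OH)D of 22 ng/ml; mean plateau in the intensive arm of 58 ng/ml; time constant of the rise 1.5, 3 or 6 months. For compliance, the unnamed quantile is taken as the top quarter, with a score that rises or falls by 1 between-woman SD.

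**Illustration by hand.** Take a woman with baseline 22, her own plateau at 65 and a time constant of 3 months. Her value at month m is 65 − 43·exp(−m/3), which gives 22, 49.2 and 59.2 at months 0, 3 and 6.

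- Disease-free to month 33: the mean of months 27, 30 and 33 is 65.0, so she is in the ≥60 group.
- Recurrence at month 6: (22 + 49.2 + 59.2)/3 = 43.5, so she is not in the ≥60 group.
- Recurrence before month 3: baseline only, 22, so she is in the ≤30 group.

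Her response to treatment is the same in all three cases. Only the timing of recurrence moves her.

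**How many recurrences are early.** Under a constant hazard with 3-year risk p, the share of 33-month events that fall by month m is [1 − (1−p)^(m/36)] / [1 − (1−p)^(33/36)].

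- p = 15%, m = 6: 0.0267/0.1384 = 19%.
- p = 15%, m = 12: 0.0527/0.1384 = 38%.
- m = 12 at p = 20%: 0.0717/0.1850 = 38.8%; at p = 10%: 0.0345/0.0921 = 37.5%.

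**Simulation with no true effect**, 800 trials per scenario. The nominal rate is 2.5% in each direction.

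| Scenario | Median HR | False protective | False harmful |
|---|---|---|---|
| 25(OH)D ≥60 vs ≤30, values end at recurrence, time constant 1.5 months | 0.43–0.44 | 48–75% | 0% |
| same, 3 months | 0.36 | 66–90% | 0% |
| same, 6 months | 0.24 | 87–99% | 0% |
| 25(OH)D, 3 months, visits continue to month 33 | 1.01 | 2.0–2.8% | 1.1–1.9% |
| Marker without time trend, median split | 1.00–1.01 | 2.6–3.0% | 2.4–2.5% |
| Compliance score rising, top quarter vs rest | 0.66–0.75 | 15–33% | at most 0.1% |
| Compliance score falling, top quarter vs rest | about 2.2 | 0% | 92–95% |
| 25(OH)D, month-12 landmark | 0.99–1.00 | 2.8–3.3% | 2.1% |

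The first three rows cover 3-year recurrence of 10% to 20%; the others cover 15% and 20%. At 15% recurrence and a 3-month constant, the false contrast is 9.1% events (≥60) against 23.5% (≤30). The simulation did not model reverse causation.

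**The case against.** The strongest reply is that the article nowhere stops visits at recurrence. Recruitment and randomization schedules them to month 33, and the analysis is by intention to treat. On that literal reading the immortal-time part goes: the null hazard ratio for 25(OH)D returns to 1.01. This stands, but it does not rescue the rule. The values then post-date the event, and any woman who recurs and leaves is missing because of her outcome.

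A second reply is that a reader might infer that all four analyses will show strong false protection. The documents do not support that. A marker without a time trend, as glucose or insulin may be, shows no immortal-time bias, and waning compliance gives false harm. The strong protective bias is shown only for 25(OH)D with values ending at recurrence, and its size rests on assumed trajectories.

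A third reply concerns the models under Secondary analyses. The sentence there does not say when each predictor is measured. With baseline predictors the fault does not arise, so the criticism reaches those models only where a predictor is post-baseline.

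Finally, these are non-randomised comparisons listed as sensitivity analyses. That is right and limits the seriousness. It is not a case of detail left to a fuller document, because the article states the rule.

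**Conclusion.** The point holds in a limited form. The last-visits rule forms groups from values measured after the DFS clock has started, and none of its three readings gives a valid comparison. Whether the result is falsely protective, null or falsely harmful depends on two things the article does not give: whether visits continue after recurrence, and how each marker moves over time. The largest shown effect is for the planned 25(OH)D contrast with values ending at recurrence: a null hazard ratio of about 0.24 to 0.44, with false protective significance in 48% to 99% of trials. This rests on a constant hazard, 10% to 20% recurrence at 3 years and the assumed rise in 25(OH)D.

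A reader might also infer that the trial's main result is compromised. It is not: the log-rank comparison by randomised arm does not use these groups. The rule should be corrected before analysis, but it is not a threat to the primary conclusion.

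**What to change.** Replace the last-three-visits rule under Sensitivity analyses with one of these:

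- **Month-12 landmark.** Classify each woman by the mean of months 6, 9 and 12 for markers taken three-monthly, and by the month-12 value for insulin. Count DFS from month 12 in women recurrence-free then.
- **Time-updated Cox model.** Use only values measured before each event time.

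Label the results as associations, since women are not randomised to the level they reach. Under Secondary analyses, apply the same rule only where a predictor is measured after baseline.

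The cost is wording; the data are already collected. The landmark drops events before month 12, about 38% of those by month 33 under a constant hazard. In the simulation at 15% recurrence, the 25(OH)D landmark contrast rests on about 15 events (84 × 0.090 + 78 × 0.091 = 14.7), so it would be imprecise. The time-updated model does not lose the early events.
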